### Baseline characteristics

All known potential confounders will be measured at baseline, including sex, age, education level, marital status, and smoking status of partner and other household members. Thus, comparisons of the intervention and control groups will be performed both unadjusted and adjusted for these known confounders. This second adjusted analysis will control for any maldistribution after randomisation of the confounders between the two groups.

### Treatment effects

Analysis of the primary outcome will involve comparing the quit rate between the two groups. Simple unadjusted rates and 95% confidence intervals will be obtained in the first instance, with subsequent multiple regression analysis adjusting for other variables. Two forms of regression analysis will be considered for the primary outcome - logistic and Cox proportional hazard. Analysis of secondary outcomes will be conducted using standard statistical procedures applicable to categorical or continuous data. All tests of significance will be two-tailed.

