### Hypothesis

A culturally appropriate, multidimensional, intensive smoking cessation intervention, provided by trained Aboriginal researchers, will be more effective than current standard practice in achieving and sustaining cessation to tobacco consumption among Aboriginal peoples and Torres Strait Islanders.

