### Study design

This study is a parallel, randomised controlled study. Participants are randomly allocated to one of two study arms: the 'intervention' group who participates in the BOABS program over 12 months, or the control group who are allocated to 'usual care' (i.e. they do not participate in the BOABS program). Aboriginal researchers are trained to deliver the BOABS program, the goal of which is to help Aboriginal people quit smoking. Data collection occurs at baseline (when participants enrol in the study), and at six and 12 months following enrolment. The primary outcome of interest is the proportion of subjects who self-report smoking cessation with urinary cotinine validation at 12 months. Figure 1 outlines the flow of participants through the study.

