#### Participants assigned to intervention group

Participants allocated to the intervention group also receive the usual health service-provided smoking cessation support, as above. In addition to this they are provided with smoking cessation counselling at face-to-face visits, which will be scheduled weekly for the first four weeks, monthly to 6 months and two monthly to 12 months. During the intervention the Aboriginal researchers are to concentrate on smoking cessation. Face-to-face follows up can take place at the clinic or other location suitable to the participant (e.g. home, work). While face-to-face contact is the default option, this may have to be adjusted if a participant's circumstances makes this difficult (e.g. a full-time worker may be offered phone contact for some of the follow up visits). If a participant does not attend for a follow up visit, the Aboriginal researcher is to initiate active follow up within 48 hours through phone or home visit to determine the reason for non-attendance and where possible determine solutions to encourage ongoing participation.

Participants in the intervention group are also encouraged to participate in a monthly smoking cessation support group, which include: 1) additional smoking cessation support and advice including cognitive and behavioural approaches to 'quitting'; 2) opportunities for information sharing/sharing of barriers and solutions; 3) a light healthy meal and 4) information sharing and advice on other aspects of health and well-being including management and prevention of common chronic diseases, which will be delivered by appropriately trained people. The group therapy occurs at both sites. This is a rolling group, with participants continually entering and leaving the group.

Content to be delivered by Aboriginal researchers:

• Individual

○ Motivational interviewing (e.g. what do you like/do not like about smoking)

○ Triggers for smoking/diversions & strategies to deal with them

○ Action plans - preventing and dealing with short term relapses (termed 'slipups')

○ Discussion regarding the positives of smoking cessation (e.g. saving money)

○ Pharmacotherapy (e.g. NRT)

○ Identification of factors driving smoking and case management to link participants to additional non-health service, community-based support agencies (e.g. alcohol counselling)

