### Outcome measures

Primary endpoint:

• The proportion of participants who were not smoking tobacco at 12 months as determined by self-report and urinary cotinine level consistent with no recent tobacco consumption [26].

Secondary endpoints:

• The proportion of participants who were not smoking at 6 months as determined by self-report.

• The proportion of participants reporting excellent or very good health using a self-reported health questionnaire [27].

• The proportion of participants who reported 20% or greater reduction in the number of cigarettes smoked each week.

• Process evaluation indicators: a mix of quantitative and qualitative measures to assess how well the intervention program was implemented according to the protocol e.g. number of 'face-to-face' meetings completed, challenges and solutions in delivering the program.

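### Cox regression is listed beside logistic regression for a reversible yes/no status at 12 months; it answers a different question, and neither is named as the adjusted primary model

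*Protocol article*

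**What the plan says.** All places are in the protocol article.

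- **Outcome measures** defines the primary endpoint as "The proportion of participants who were not smoking tobacco at 12 months as determined by self-report and urinary cotinine level" consistent with no recent smoking. The 6-month measure is a secondary endpoint: "The proportion of participants who were not smoking at 6 months as determined by self-report". It has no cotinine check.
- **Treatment effects** begins with the plain comparison: "Simple unadjusted rates and 95% confidence intervals will be obtained in the first instance". Adjusted regression follows, and for that step "Two forms of regression analysis will be considered for the primary outcome - logistic and Cox proportional hazard". Neither model is designated, and no event or event time is given for Cox.
- **Study design** gives one outcome schedule, without distinction by arm: "Data collection occurs at baseline (when participants enrol in the study), and at six and 12 months following enrolment".
- **Participants assigned to intervention group** adds counselling visits, "scheduled weekly for the first four weeks, monthly to 6 months and two monthly to 12 months". That is about 12 contacts (4 weekly, 5 monthly, 3 two-monthly). The control group has no comparable scheduled contact.
- **Inclusion criteria** admits people who stopped smoking up to two weeks before recruitment. The intervention content plans for slip-ups, and **Protocol deviations** describes a model in which smokers quit and relapse several times before lasting success.
- **Blinding** says that only the cotinine laboratory staff are unaware of allocation.

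**The concern.** The endpoint is a status at a fixed time. Cox regression needs an event that happens once and a time at which it happens. The natural candidate is the first reported quit, but that differs from the endpoint in three ways.

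1. A person who quits early and relapses is a success for Cox and a failure for the endpoint.
2. A quit recorded at 6 months rests on self-report alone, in a trial where participants and researchers know the allocation. The cotinine confirmation that defines the endpoint is bypassed.
3. Some participants may already be in the event state at time zero.

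The two models can therefore disagree, and the text leaves open which one supplies the adjusted result for the primary outcome. The hypothesis is that the program is "more effective than current standard practice in achieving and sustaining cessation to tobacco consumption". Time to first quit bears on achieving cessation but not on sustaining it. An early, short-lived effect could be presented as a positive adjusted primary result.

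**Working it through.** The plan states no figure for the Cox analysis, so there is none to reproduce. The check asks what Cox would return under two ways of dating quits, compared with the 12-month proportions.

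**Inputs from the document:** 120 intervention and 240 control (target sample size); planning quit rates of 3% and 13%; two-sided alpha 0.05; outcome data at 6 and 12 months; about 12 intervention visits. **Assumptions, not in the document:** the 6-month rates in step 2, and the weekly relapse probabilities in steps 1 and 3 (0 to 0.25, same in both arms).

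**Step 1. Common schedule, identical quit processes.** A weekly quit/relapse process, the same in both arms, was simulated (800 trials per setting), with Cox on time to first quit seen at 6 or 12 months. Rejection rates were 2.0% to 4.5% with 3% abstinent at 12 months and 3.6% to 6.4% with 13%; hazard ratios were about 1.0. There is no material false-positive problem here.

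**Step 2. Common schedule, early effect gone by 12 months.** Assume 13% v 3% abstinent at 6 months, 3% in both arms at 12 months, and 12-month status independent of 6-month status. Expected log-rank quantities, with E = D × n1/N and V = D × (n1 × n0/N²) × (N − D)/(N − 1):

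| Time | At risk (int., ctrl) | First quits (int., ctrl) | E (int.) | O − E | V |
|---|---|---|---|---|---|
| 6 months | 120, 240 | 15.6, 7.2 | 22.8/3 = 7.6 | 8.0 | 4.76 |
| 12 months | 104.4, 232.8 | 3.13, 6.98 | 3.13 | 0 | 2.10 |

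- z = 8.0/√(4.76 + 2.10) = 8.0/2.62 = 3.05.
- Power is about Φ(3.05 − 1.96) = Φ(1.09) = 0.86, that is, about 85%.
- Hazard ratio: the one-step estimate is exp(8.0/6.86) = 3.2. The Cox score equation with Breslow ties, 15.6 + 3.13 = 22.8 × 120θ/(120θ + 240) + 10.12 × 104.4θ/(104.4θ + 232.8), is solved at θ = 2.7. So it is about 3, depending on the handling of ties.
- Primary endpoint: 3% of 120 = 3.6 against 3% of 240 = 7.2, a difference of zero.

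Cox would usually report a benefit where the stated endpoint shows none.

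**Step 3. Intervention quits also dated from counselling visits, identical quit processes.** The simulation is as in step 1, but with the intervention arm seen at all 12 visits and control at 6 and 12 months only.

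| Weekly relapse (assumed) | Cox rejects, 3% abstinent | Median HR | Cox rejects, 13% abstinent | Median HR |
|---|---|---|---|---|
| 0 | 2.8% | 1.00 | 5.2% | 1.03 |
| 0.02 | 5.5% | 1.26 | 18.1% | 1.28 |
| 0.05 | 16.6% | 1.54 | 65.4% | 1.67 |
| 0.10 | 56.1% | 2.26 | 99.8% | 2.50 |
| 0.25 | 98.9% | 3.82 | 100% | 4.52 |

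The test of 12-month proportions rejected in 3.4% to 6.0% of trials across all the settings of steps 1 and 3.

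**The case against.** The strongest reply is that the main comparison is already fixed. Unadjusted 12-month rates with intervals come first, regression is a later adjustment step, and Cox is only to be considered. Event and censoring rules commonly sit in a statistical analysis plan or full protocol, neither of which is shown. Moreover, if every participant were given the same 12-month time, the Cox hazard ratio with Breslow ties would simply equal the risk ratio, which is harmless.

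Most of this stands, and it limits the severity. The missing event definition is not itself the point. What remains is that the model named in the text does not fit the endpoint defined in the text. Giving everyone one common time would make Cox redundant, and the article does not say that this is intended.

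A reader might also infer that, because the arms are contacted about 12 times against twice, Cox is bound to favour the intervention even when there is no effect. The document does not support that. It gives both arms one outcome schedule, and nothing in it says that smoking status at counselling visits enters the outcome analysis. On the common schedule, type I error is about nominal. The inflation in step 3 arises only if visit-level quits are used, and its size depends on a relapse rate that the document does not give; with no relapse there is none. It also assumes full attendance at the counselling visits.

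**Conclusion.** The point holds as a mismatch between model and endpoint, together with an undesignated choice between two adjusted models. It does not hold as a claim that the planned analysis would show a benefit under the null.

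On the schedule that the document describes, the risk is that Cox answers a different question. Under the assumed early effect (13% v 3% at 6 months, equal at 12), it gives a hazard ratio of about 3 and power of about 85% while the primary endpoint is identical in the two arms. The 6-month rates and their independence from 12-month status are illustrative assumptions. The false-positive range of about 3% to 99% at 3% abstinence is conditional on a use of counselling-visit data that the text neither plans nor rules out, and on assumed weekly relapse of 0 to 0.25. The unadjusted 12-month comparison is unaffected.

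**What to change.** In Treatment effects, delete Cox regression for the primary outcome. State that the primary analysis compares the 12-month cotinine-confirmed proportions between arms with a 95% confidence interval, and that logistic regression on the same status is the single adjusted model.

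If a time-to-quit analysis is still wanted, label it exploratory, define the event, and take status only at the 6- and 12-month points common to both arms. A binary secondary endpoint of abstinence at both 6 and 12 months, with cotinine confirmation at 12, would speak to sustained cessation from data already collected. It is optional and the correction does not depend on it.

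The cost is a change of analysis wording; no new data are needed.

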### Procedures to account for missing data

Analysis will be on an intention-to-treat basis. A sensitivity analysis will be conducted for all participants who are lost to follow-up, with the assumption that none of them quit compared to all of them quitting at 12 months. An additional analysis will assume that participants in the intervention group who cannot be followed up will have the same quit rate as the control group. Participants who die during the trial will be excluded from the analysis.

### Ethics

The trial will be conducted in compliance with the protocol, the principles of Good Clinical Practice, the NHMRC National Statement on Ethical Conduct in Human Research (2007), NHMRC Australian Code for the Responsible Conduct of Research (2007), and NHMRC Values And Ethics: Guidelines For Ethical Conduct In Aboriginal And Torres Strait Islander Health Research (2003) [29-31]. This trial has ethical approval from The University of Western Australia HREC and the Western Australian Aboriginal Health Information and Ethics Committee, and support from the Kimberley Aboriginal Health Planning Forum Kimberley Research Subcommittee.

### Trial management

The Project Manager is responsible for the day to day management of the trial. The Project Manager's responsibilities include meeting regularly with the Aboriginal researchers and investigators, keeping copies of all documentation including details of standard care at DAHS and OVAHS and any changes to the standard Kimberley Smoking Cessation Protocol, making sure that the data is collected and stored properly, overseeing the recruitment of participants to the study, ensuring the randomisation and allocation process is complying with the protocol, recruit participants, administer the questionnaires and carry out follow ups if required, ensure project targets for participant enrolment and follow up are being met, and provide administrative support for the project.

The Aboriginal researchers will recruit participants, administer the questionnaires, carry out follow ups, keep copies of the questionnaires in a locked filing cabinet, and organise weekly case conferences with a clinic general physician and review all active participants in the intervention group.

## Protocol deviations

### Modification of the participant selection criteria and removing the Stages of Change model from the Protocol

A major selection criteria for this trial was that potential participants were required to be at the ready stage of the Stages of Change Model (i.e. considering quitting smoking soon / within the next 30 days). This model hypothesises that the process of someone quitting smoking is cyclical with smokers passing through the stages of NOT READY, UNSURE, READY, and quitting (MAINTENANCE), rather than a discreet event [32-34]. In this model smokers are thought to cycle through the stages of being ready, quitting and relapsing 3 to 4 times before successfully quitting long-term. The proponents of this model also suggest that interventions should be designed according to the stage the participants are at [33].

We found that this criterion is too restrictive and that very few Aboriginal peoples and Torres Strait Islanders in Derby and Kununurra fulfil the criteria for being at the 'READY' to quit smoking stage as we operationalised it, although a much larger number are interested in quitting. As detailed in the background, studies suggest that quitting can occur in what appear to be relatively unmotivated smokers and can be encouraged by intervention and the use of pharmacotherapy (reviewed in [16]). We therefore applied to the DSMC and supervising HREC to modify the selection criterion to include a wider range of people who are thinking of cutting down or quitting, so that we would be more likely to meet our sample size and to access a broader more appropriate target population.

## Discussion

Aboriginal peoples and Torres Strait Islanders smoke at much higher rates than non-Indigenous people and smoking is an important contributor to increased disease, hospital admissions and deaths in Indigenous Australian populations. Quit smoking programs in Australia have not had the same impact on Indigenous Australian smokers as on non-Indigenous smokers. A range of strategies have been used to encourage Indigenous people to quit smoking however there have been few good quality studies that show what approaches work best. More evidence of strategies that could work more widely in Indigenous Australian primary health care settings is needed if good policy is to be developed and implemented. This culturally appropriate, multidimensional, intensive smoking cessation intervention, which is provided by trained Aboriginal researchers in a remote Australian setting, has been designed to provide high quality evidence as to its efficacy. Part of the process of implementing high quality research pertinent to the health care needs of Aboriginal peoples and Torres Strait Islanders and to supporting a culture of translating such research into sustainable health care delivery requires support from the communities and health services involved. The involvement of Aboriginal community-controlled health services in projects such as this ensures local ownership, facilitates implementation, aids knowledge translation and builds local research capacity. The addition of a process evaluation of this study will provide important information about the type of research models that can work within ACCHS.

## Abbreviations

ACCHS: Aboriginal community controlled health service; BOABS: Be our ally, beat smoking; DAHS: Derby aboriginal health service; DSMC: Data safety and monitoring committee; HREC: Human research ethics committee; NRT: Nicotine replacement therapy, available in a range of forms such as patch, gum lozenges, tablets and nasal spray; NHMRC: National health and medical research council; OVAHS: Ord valley aboriginal health service; RCT: Randomised controlled trials.
